## Materials and equipment

### Smartphone application

The smartphone application will contain four key features:

Questionnaires: the mobile application will link participants to Qualtrics questionnaires, including video stimuli. These will be presented to the participants at in-take, during the daily intervention, and at post-intervention assessment;Notifications: a push-notification system will remind participants to view the stimuli and complete the questionnaires every day, while the intervention is in progress;Communication with the research team: an email link will allow participants to contact the research team directly;Personalized progress reports: participants will receive a link to a report of their post-intervention progress once the study is complete.

### Measures

#### Demographic questionnaire

Participants will be asked to provide demographic information, such as gender, native language, education level, age, ethnicity, and country of residence.

#### Intake screeners

##### Assessment of Compulsive Buying Behavior

The Clinical Screener (CBCS; Faber and O'Guinn, 1992) is one of the most validated and replicable self-report scales measuring compulsive buying behavior, having been found to correctly classify 88% of compulsive buyers (Faber and O'Guinn, 1992). The CBCS contains seven statements that respondents are required to rate their agreement with (1 = Strongly disagree to 5 = Strongly agree) (e.g., “If I have any money left at the end of the pay period, I just have to spend it”) or their frequency of experiencing given behaviors/feelings (1 = very often to 5 = never) (e.g., “Bought things even though I could not afford them”) on five-point Likert scales. A total score is calculated, and a threshold measurement determines whether an individual is considered a compulsive buyer.

Faber and O'Guinn's (1992) compulsive buying scale has, however, been criticized for only addressing the impulse control dimension of compulsive buying behavior and not the obsessive-compulsive dimension, as well as not being accommodating to buyers that have higher incomes (Ridgway et al., 2008). To compensate for these limitations, the Compulsive-Buying Index (CBI) developed by Ridgway et al. (2008) will be used in addition to the CBCS, thus presenting a more comprehensive measurement of compulsive buying behavior.

The Compulsive-Buying Index (CBI) is a well-validated measure of compulsive buying behavior (Ridgway et al., 2008). The CBI contains six items measuring two dimensions of compulsive buying; three items for obsessive-compulsive buying (e.g., “My closet has unopened shopping bags in it”) and three items for impulsive buying (e.g., “I buy things I don't need”). Responses are given on a seven-point Likert scale either indicating agreement with statements (1 = strongly disagree to 7 = strongly agree) or frequency of experiencing given behaviors/feelings (1 = never to 7 = very often). A total score is calculated, and a threshold measurement determines whether an individual is considered a compulsive buyer.

##### Assessment of Voluntary Simplicity

*Lifestyles*. The Voluntary Simplicity Lifestyles scale used in this study (VSL; Nepomuceno and Laroche, 2015) is an adapted version of Iwata's original voluntary simplicity scale (Iwata, 1997), a validated self-reported measure of the adoption of the voluntary simplicity consumer lifestyle. This adapted scale is made up of nine statements describing a number of behaviors that are consistent with a voluntary simplistic lifestyle, such as the scale item “I fully adhere to a simple lifestyle and only buy necessities.” Participants are required to rate their agreement with these statements on a five-point Likert scale (1 = definitely disagree to 5 = definitely agree), indicating the degree to which they engage in the suggested simplistic lifestyle choices.

*Involvement*. The Personal Involvement Inventory (PII; Zaichkowsky, 1994) is considered a validated context-free measure of one's motivation to be involved with certain concepts, behaviors or products. This study tailored the PII to measure consumers' voluntary simplicity involvement. Involvement is measured on a self-report semantic scale made up of 10 items. The scale can be divided into two subscales: the affective subscale (e.g., interesting, appealing) and the cognitive subscale (e.g., important, relevant). Participants will be asked to judge voluntary simplicity across all cognitive and affective adjectives. Participants rate each item along a bipolar adjective scale (e.g., “interesting” or “boring”), judging how close they deem voluntary simplicity to either opposing adjective. Responses are given on a seven-point scale and six items require reverse scoring. A total involvement score is calculated where higher scores represent higher involvement.

##### Assessment of Materialism

The Materialism Scale (MS; Richins and Dawson, 1992) is a validated self-report scale measuring materialism value. The 18-item scale measures three dimensions of materialism; success, centrality and happiness, which describe different motivations for acquiring material possessions. Six items measure success, indicating the perception that possessions are indicators of life-success (e.g., “I admire people who own expensive homes, cars, and clothes”). Seven items measure centrality, representing the general importance of acquisition and possession (e.g., “I enjoy spending money on things that aren't practical”). The last five items measure happiness, representing the perception that possession is necessary for happiness (e.g., “My life would be better if I owned certain things I don't have”). The MS is measured on a five-point Likert scale (1 = strongly disagree, 5 = strongly agree) and eight items require reverse coding. An overall scale score is calculated from the three dimensions, a higher score suggesting higher materialism than a lower score.

##### Assessment of Egoistic, Altruistic, and Biospheric Values Orientations

The Value Instrument is an adapted, validated measure of egoistic, altruistic and biospheric value orientations (de Groot and Steg, 2008). This scale is an adapted form of the Schwartz value scale (Schwartz, 1992), and consists of 13 items: five for egoistic (e.g., wealth), four for altruistic (e.g., equality), and four for biospheric (e.g., unity with nature) value orientations. Internal reliabilities for these sub-scales range from .73 to .86. As in the Schwartz value scale, participants rate the importance of the 13 items “as a guiding principle in their lives” on a nine point Likert-scale (–1 = opposed to my values, 0 = not important to 7 = extremely important). In the instructions segment, respondents are requested to vary the scores they provide each value and only rate very few of them as extremely important.

##### Assessment of Satisfaction with Life

The Satisfaction with Life Scale (SWLS; Diener et al., 1985) is a validated measure of subjective well-being, characterized by favorable psychometric properties, such as convergent validity with other similar measures, cross-cultural validity, and temporal stability (Pavot and Diener, 2008). The five-item self-report scale measures global life satisfaction by scoring participant agreement to a statement such as “I am satisfied with my life” on a seven point Likert-scale (1 = strongly disagree to 7 = strongly agree). A total score can range between five (low satisfaction) and 35 (high satisfaction) suggesting the degree of life satisfaction of the participant.

##### Assessment of Motivation

Participants will be asked to rate their motivation source and strength for taking part in the study. Motivation sources will match the aforementioned value orientations (e.g., egoistic and hedonic: “improve my well-being,” “save my money”; altruistic: “improve the lives of others around me,” “donate more to others”; and biospheric: “improve the future of the environment,” “reduce my carbon footprint”). Participants will rate their agreement with these motivations similarly to the value instrument (–1 = opposed to my motivation, 0 = not motivating to 7 = extremely motivating).

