## Design

A weeklong intervention program will test the efficacy of watching voluntary simplicity videos in reducing non-essential consumption. The first condition will promote voluntary simplicity while priming self-transcendence values and goals, and the second condition will promote voluntary simplicity while priming self-enhancement values and goals. These two interventions will be compared with a control condition which only measures participant's affective state during the intervention week. All participants will undergo baseline and post-intervention evaluations of values and goals in consumption reduction, voluntary simplicity attitudes and behaviors, spending behaviors, and life satisfaction directly before and directly following the intervention, respectively. A one-month follow up measurement will also be taken. The difference between measurements before and after the intervention will serve as our dependent variables.

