## Procedure

At baseline, all participants will download a free mobile application. Participants will complete an intake survey on Qualtrics, through a link in the mobile application. Following intake, participants will be randomly allocated to one of the three experimental conditions, and complete a battery of questionnaires measuring dependent and independent variables (see t0 in Figure 1). After baseline measurements, the intervention will commence. In the two intervention conditions, participants will watch one video daily for 6 days. Both intervention and control condition participants will complete a daily mood measurement (see t1 through t6 in Figure 1). On the last day of the intervention, participants will complete questionnaires measuring the dependent and independent variables a second time (see t7 in Figure 1). One month after intervention completion, the dependent variables will be measured again (see t_end_ in Figure 1).

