#### Post-intervention questionnaire

The effectiveness of the intervention will be measured by the difference of participants' pre- and post-intervention measurements, controlling for covariates. Therefore, all intake questionnaires will be repeated in the post-intervention phase. Along with these repeated scales, several additional measures will be administered.

Two additional questions will measure participants' attitude toward the videos. The first item will measure whether participants would recommend the video to friends with a similar goal (i.e., “Would you recommend these videos to a friend who also wanted to reduce their non-essential consumption?”). The second item will measure participants' intention to continue watching similar videos online (i.e., “Would you watch similar videos online?”). Participants would be required to indicate their answer on a nine-point scale (0 = not at all to 8 = definitely) for both questions. Lastly, an open-ended question will allow participants to share what they thought was interesting, difficult, or helpful during the one week of intervention.

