### Changes in values and motivations

Using a repeated-measures ANOVA, with *post-hoc* contrasts, we will also compare in-take measurements of participants' values and motivations to the two post-intervention measurements. Thus, we will test whether exposure to the intervention stimuli affected consumer values and motivations directly. We expect participants in the self-transcendence condition to show an increase in biospheric values and motivations at t7, while participants in the self-enhancement condition will show an increase in egoistic values and egoistic and hedonic motivations at t7. Control condition participants are not expected to show a significant change in either values or motivations during the intervention. This measurement will serve as a manipulation-check. We will also explore whether the manipulation persists at t_end_, one month following the intervention.

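### The motivation scale is described as asking about taking part in the study, so its change is an ambiguous check on primed consumption-reduction goals, and hedonic content has no other described measure

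*Protocol article*

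**What the plan says.** All references are to the protocol article.

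- *Assessment of Motivation* gives the question as: "Participants will be asked to rate their motivation source and strength for taking part in the study". On the items it says: "Motivation sources will match the aforementioned value orientations (e.g., egoistic and hedonic", followed by altruistic and biospheric examples. The response scale starts at -1 (opposed) and continues "0 = not motivating to 7 = extremely motivating".
- *Post-intervention questionnaire*: "all intake questionnaires will be repeated in the post-intervention phase". No change to the motivation question is mentioned.
- *Changes in values and motivations* compares intake values and motivations with both later measurements by repeated-measures ANOVA and calls this the manipulation check. Biospheric values and motivations should rise in the self-transcendence arm, and "participants in the self-enhancement condition will show an increase in egoistic values and egoistic and hedonic motivations at t7". Persistence at one month is to be explored.
- *Design* names the construct to be assessed before and after: "baseline and post-intervention evaluations of values and goals in consumption reduction".
- *Assessment of Egoistic, Altruistic, and Biospheric Values Orientations* gives the make-up of the Value Instrument: "five for egoistic (e.g., wealth), four for altruistic (e.g., equality), and four for biospheric (e.g., unity with nature) value orientations".

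**The concern.** A manipulation check has to measure what the manipulation is meant to move. The videos are meant to move the participant's goals for buying less. The scale, as described, asks about motivation for being in the study, which is a related but different object. *Participant commitment through feedback* itself lists attractions of participation, such as personal progress feedback and a 100-euro lottery, that are not environmental or personal goals for consuming less.

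There is also a question of time frame. Someone who enrolled to save money and was then persuaded by the environmental videos could reasonably give the same answer as at intake, because the reason for enrolling has not changed. Someone else could answer the same question with today's goals. The analysis cannot tell the two apart.

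The second main research question asks whether self-enhancement goals work as well as self-transcendence goals. If the motivation ratings do not move, or move in one arm only, the team could not say whether a prime failed or whether participants restated why they took part. The problem is uneven between the arms, because the hedonic part of the self-enhancement prime has no second described measure.

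**Working it through.** No sample size, power or error rate enters this point. The check sets the relevant sections side by side and counts what each instrument covers.

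**1. Construct.** *Design* calls for values and goals in consumption reduction. *Assessment of Motivation* asks about taking part in the study. The wording of the two does not match.

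**2. Time frame.** The article says when it changes a question's time frame: for the mood scale, *Short Mood Scale (PANAS)* states that the phrasing will be revised to refer to the present. No such statement is made for the motivation scale, so the article gives no reason to think the question differs at t7 or one month.

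**3. Coverage of the Value Instrument.** 5 egoistic + 4 altruistic + 4 biospheric = 13 items, the stated total. That leaves 13 - 13 = 0 hedonic items.

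**4. Predicted rises at t7, by instrument** (from *Changes in values and motivations*):

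| Arm | Predicted rise | Instrument | Counterpart in the other instrument |
|---|---|---|---|
| Self-transcendence | Biospheric values | Value Instrument | Motivation scale |
| Self-transcendence | Biospheric motivations | Motivation scale | Value Instrument |
| Self-enhancement | Egoistic values | Value Instrument | Motivation scale |
| Self-enhancement | Egoistic motivations | Motivation scale | Value Instrument |
| Self-enhancement | Hedonic motivations | Motivation scale | None described |

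Counting egoistic and hedonic motivations separately, there are 2 value targets and 3 motivation targets, 5 in all. Three of the five rest on the question about taking part, and one of those three, the hedonic one, has no counterpart.

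**5. Hedonic content is part of the prime.** *Surveys and intervention* says the self-enhancement visuals prime hedonic as well as egoistic values, and the sample script for that arm refers to being less stressed. *Self-transcendence and self-enhancement in minimalism videos* labels stress reduction as hedonism. What the check lacks a second measure for is therefore an intended component of the arm.

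**6. Presentation of the items.** *Assessment of Motivation* places the well-being and money-saving examples under one joint egoistic-and-hedonic label. The article does not say whether they will be scored together or apart.

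**The case against.** The strongest case on the other side has five parts.

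- **The scale may capture current goals.** A reader might infer that the scale asks why people joined, so that it cannot register change and the expected change is zero in every arm. The document does not support that. It speaks of taking part, which is ongoing, and t7 falls while participants are still in the programme: "On the last day of the intervention, participants will complete questionnaires measuring the dependent and independent variables a second time". The response anchors are in the present and the items are goal statements that videos could shift. Recruitment is also restricted to people who want to consume less, so reasons for taking part and reasons for consuming less will overlap. This stands. It reduces the point from a scale that cannot show change to one whose change is ambiguous, less so at t7, where the predictions lie, and more so at one month, which is exploratory.
- **The question is described, not quoted.** Only the items appear verbatim, and the administered form is not shown. This stands, and it is why the point concerns the scale as described.
- **Other checks exist.** Each arm keeps a value-based check from an instrument with a different question. Experts also review the video checklists, and a pre-test rates whether the presenter promoted the intended values. This stands in part. The Value Instrument rates general life principles, not goals for consuming less, and has no hedonic items. The pre-test uses a different sample and rates the message, not what participants took up.
- **A separate goal measure may exist.** *Consumption reduction—behavior* lists personal goals to reduce consumption apart from motivations among its intake control variables. A reader should therefore not conclude that goals are measured nowhere else, only that no other goal instrument is described.
- **The consequence is limited.** The comparison between the two video arms is labelled exploratory, and the outcomes do not depend on this scale. This stands.

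**Conclusion.** The point holds in a limited form. As described, the motivation scale asks about participation, while its change is used as part of the manipulation check for consumption-reduction goals. A change, or its absence, is therefore open to two readings: reasons for participating, possibly recalled, or current goals. Three of the five predicted targets are affected, and the hedonic one has no other described measure.

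No numerical size can be attached, because the documents do not indicate how participants would interpret the question. The conclusion assumes that the administered wording follows the article's description and is the same at each occasion. If the form already asks about current goals for reducing consumption, the point reduces to a correction of the description and the separate reporting of hedonic items.

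A reader might also infer that the arm comparison is invalid. It is not: the randomised comparisons on consumption, intent and life satisfaction stand. What is weakened is the explanation of any difference, or lack of one, in terms of the primed goals.

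**What to change.** - Keep the items and the -1 to 7 scale. Use one stem, worded identically at t0, t7 and one month, that asks how strongly each item currently motivates the participant to reduce non-essential consumption.
- Report the hedonic items (such as the well-being item) separately from the egoistic ones (such as the money-saving item), so that the hedonic part of the prime has its own check.
- If reasons for taking part are wanted as a covariate, keep that version at intake only.
- State the stem in the measures section, as is done for the mood scale.

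The cost is one reworded stem in the online form and, if the intake version is kept, a few extra items at t0 (the article gives six examples, two for each of three groupings). No extra participants or visits are needed. The change has to be made before launch, because a baseline collected with one stem cannot be compared cleanly with later answers to another.

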##### Assessment of Consumption Related Attitudes and Behaviors

*Shopping intention*. Shopping intention will be measured by adapting the three items of the eight-point semantic scale of behavioral buying intention (Baker and Churchill, 1977). The original items were intended to measure participants' intention to buy a specific product. In this study, the items will be adapted to suit the context of the non-essential product buying intention. Participants will be asked to think of a type of product they would normally buy, which is non-essential (e.g., clothing, sweet snacks, coffee). Then, they will be asked about their purchase intent for this product, for example: “Would you buy this non-essential product within the next seven days?” In response to the question, participants should indicate their intention on an eight-point semantic scale of “yes—definitely” to “no—definitely not.”

*Buying frequency and behavior*. Two questionnaires (see Appendix B) measuring shopping frequency (Section A, seven items) and average weekly non-essential expenditures (Section B, two items) will be administered to participants. The order of the items within both sections will be randomized. Responses for five of the total nine items of the two questionnaires will be given on a six-point Likert scale, ranging from zero to five (e.g., “How likely are you to shop for something you need in the coming week?”) that will be averaged within each section. The remaining four items will require an open response by the participant (e.g., “How many times do you typically go shopping in a week?”).

#### Intervention questionnaire

##### Short Mood Scale (PANAS).

The Short Form Positive and Negative Affect Schedule (I-PANAS-SF; Thompson, 2007) is a short version of the widely-used measure of the variation in affect, the Positive and Negative Affect Schedule (PANAS; Watson et al., 1988). PANAS is a well-validated measure of affect with strong psychometric properties (Watson et al., 1988; Crawford and Henry, 2004), demonstrated cross-culturally (e.g., Joiner et al., 1997) and within both community and clinical samples (Leue and Beauducel, 2011). The I-PANAS-SF is a 10-item self-report scale that is divided into two subscales, Negative Affect (NA; afraid, ashamed, hostile, nervous, and upset) and Positive Affect (PA; active, alert, attentive, determined, and inspired). Participants are required to judge the extent to which they experience the NA and PA adjectives on a seven-point Likert scale (0 = never to 7 = always) in response to the statement: “Thinking about yourself and how you normally feel, to what extent do you generally feel.” This phrasing will be revised to address the current moment.

